# Ventricular tachycardia in ischemic cardiomyopathy; a combined endo-epicardial ablation as the first procedure versus a stepwise approach (EPILOGUE) – study protocol for a randomized controlled trial

**DOI:** 10.1186/s13063-015-1005-6

**Published:** 2015-10-29

**Keywords:** Epicardial ablation, Ischemic cardiomyopathy, Ventricular tachycardia

## Abstract

**Background:**

The role of epicardial substrate ablation of ventricular tachycardia (VT) as a first-line approach in patients with ischemic heart disease is not clearly defined. Epicardial ablation as a first-line option is standard for patients with nonischemic dilated cardiomyopathy and arrhythmogenic right ventricular cardiomyopathy. Several nonrandomized studies, including studies on patients with ischemic heart disease, have shown that epicardial VT ablation improves outcome but this approach was often used after a failed endocardial approach. The aim of this study is to determine whether a combined endo-epicardial scar homogenization as a first-line approach will improve the outcome of VT ablation.

**Methods/Design:**

The EPILOGUE study is a multicenter, two-armed, nonblinded, randomized controlled trial. Patients with ischemic heart disease who are referred for VT ablation will be randomly assigned to combined endo-epicardial scar homogenization or endocardial scar homogenization only (control group). The primary outcome is recurrence of sustained VT during a 2-year follow-up. Secondary outcomes include procedural success and safety.

**Discussion:**

This study is the first randomized trial that evaluates the role of a combined endo-epicardial scar homogenization versus endocardial scar homogenization for the treatment of ischemic scar-related VT.

**Trial registration:**

NL4816807814v02

## Background

Ventricular tachycardia (VT) is an important clinical sequela after a myocardial infarction and may be associated with sudden cardiac death [1]. The introduction of the implantable cardioverter defibrillator has provided an important tool in the prevention of sudden cardiac death. However, a significant proportion of patients experience multiple appropriate implantable cardioverter defibrillator shocks due to sustained VT. Catheter ablation of VT is useful to reduce the burden of VT. The threshold for VT ablation has lowered in recent years, mainly as a result of technological advancements and increased experience [2–4]. The endocardial approach has been the preferred first-line approach for VT ablation in patients with ischemic heart disease.

Recent studies suggest that 12–17 % of all VTs in a mixed population of ischemic and nonischemic cardiomyopathies have an epicardial origin [5, 6]. Epicardial VTs have been observed in 10 % of post-infarction VTs [7]. These numbers may be underestimated, considering the moderate outcomes of endocardial VT ablations [8, 9]. In experienced centers, epicardial VT ablation has an acceptable risk-to-benefit ratio [6, 10]. Current recommendations for scar-related VT suggest that patients with ischemic heart disease can benefit from an epicardial approach if an endocardial ablation fails [11].

The aim of this randomized trial is to determine whether combined endo-epicardial scar homogenization as a first-line approach will improve the outcome of VT ablation in comparison with endocardial scar homogenization only.

## Methods/design

### Study design

The EPILOGUE study is a multicenter, two-armed, nonblinded, randomized controlled trial. Patients will be randomized to endocardial scar homogenization or endo-epicardial scar homogenization (Fig. 1). The study period is 2 years after the index procedure. All participating centers are tertiary referral centers for VT ablation with experience in epicardial ablation.

**Fig. 1 Fig1:**
[figure not shown]
EPILOGUE study flow chart. *Normal recordings are defined as not more than three sharp and discrete deflections from baseline, amplitude >1.5 mV, duration >70 ms or amplitude-to-duration ratio >0.046. FU, follow-up; VT, ventricular tachycardia

### Study population

All patients with a history of ischemic heart disease who are referred for VT ablation will be considered for inclusion. Patients can be included if they meet all of the following inclusion criteria:Age ≥18 years;History of ischemic heart disease;Presence of or planned-for implantable cardioverter defibrillator soon after VT ablation.

Patients will be excluded if they meet any of the following criteria:Presence of unstable angina;Acute myocardial infarction <30 days (or in case of incessant VT, <14 days);Absence of visualization of coronary anatomy (coronary angiogram or computed tomography);Presence of significant coronary stenosis clinically relevant for intervention;Presence of mobile left ventricular thrombus;Presence of aortic or mitral mechanical valve prosthesis;Previous pericarditis;Previous coronary artery bypass graft;Other factors that could potentially lead to pericardial adhesion (e.g., thoracic radiation therapy);Contra-indication for general anesthesia.

### Ethics

The study protocol was approved in February 2015 by the Medical Ethical Committee (2014–248) Erasmus Medical Center, Rotterdam, The Netherlands. Informed consent will be obtained from each participant.

### Primary and secondary outcomes

The primary outcome of this study is recurrence of sustained VT (defined as appropriate implantable cardioverter defibrillator therapy or VT >30 s duration) within 2 years. We will use a blanking period of 1 week after the ablation procedure. The secondary outcome parameters will be acute procedure success and procedure-related major complications. Procedural success will be defined as complete success if there is noninducibility of any sustained monomorphic VT. Partial success will be defined as noninducible clinical VT but inducible polymorphic VT, or VT with a cycle length <200 ms. Procedural failure will be defined as a spontaneous occurrence of VT or inducible clinical monomorphic VT.

Furthermore, the following data will also be determined: procedure time, fluoroscopy time, radiofrequency ablation time, time to recurrence of the ventricular arrhythmia, number of appropriate implantable cardioverter defibrillator therapies on follow-up, number of VT-related hospitalizations, freedom of antiarrhythmic drugs on follow-up, repeated (epicardial) ablation procedures, evidence of an incessant VT or VT storm during follow-up, and mortality.

### Study groups

This study has two study arms, the endocardial approach only and the combined endocardial and epicardial approach (combined approach). Crossover is not allowed during the first procedure. When a patient is randomized to the combined approach and the epicardial access is unsuccessful, this is considered a screening failure.

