#### Pericardial access

In patients undergoing epicardial ablation, before ablation and systemic heparinization, subxiphoid pericardial access will be obtained by fluoroscopic guidance (lateral plane). Using a Tuohy needle, small amounts of contrast are injected while carrying out the puncture. Guided by fluoroscopy, a guide wire is inserted into the pericardial space and an Arrow sheath is placed. An appropriate sized guiding catheter is inserted to keep the sheath open. During ablation, we will use an irrigated tip catheter. The baseline flow should be reduced to 1 ml/min. Fluid will be drawn from the pericardial space frequently during the ablation.

At the discretion of the operator, epicardial phrenic nerve capture will be performed if the origin of the VT is located in the area of the phrenic nerve. When capture is performed, a balloon is inserted and inflated to avoid phrenic nerve damage during ablation.

At the end of the procedure, a pericardial drain is inserted for 24–48 h. The operator will administer an intrapericardial steroid injection. Colchicine should be prescribed for up to 1 month, commencing on the first day after the procedure. The first day post procedure Colchicine is dosed 1 mg twice daily followed by a maintenance dose of Colchicine 0.5 mg twice daily.

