#### Ablation protocol (both groups)

If a hemodynamically tolerated VT is induced during the electrophysiological study, a standard activation or entrainment mapping is carried out. The ablation will continue until the VT is no longer inducible. Additionally, endocardial scar homogenization will be performed. Based on the substrate map, ablation will be empirically extended throughout the entire scar endocardially. Also delayed and fractionated electrograms will be targeted for ablation. If clinical VT is still inducible in the endocardial ablation-only group, an epicardial VT ablation will be performed in a ‘redo’ procedure. Epicardial mapping and ablation will be performed as described in the combined approach.

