### Sample size calculation

Sample size was calculated based on the following assumptions: a 29 % difference in primary outcome event rate (recurrence of VT) between the endocardial and epicardial group (15 %) and the control group (44 %) after a follow-up time of 2 years [9]. We calculate that a sample size of 86 patients is required to achieve an 80 % power to detect a significant difference with a (two-tailed) alpha error of 5 %. Allowing for a dropout rate of 10 %, we calculated that we would require 100 subjects.

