### Role of epicardial ablation

In 73 % of unsuccessful endocardial ablations, evidence of an epicardial substrate of VT was found [14]. To reach procedural success in VT ablation, Cesario et al. [15] found that 40 % of the patients were in need of an epicardial ablation. A recent retrospective observational study from Tung et al. [16] compared the outcomes of patients who underwent epicardial ablation with the outcomes of patients who did not. The pericardial space could not be accessed in 7 % by the percutaneous technique. The study demonstrated that at 12 months those with an ischemic substrate for VT who underwent a combined endocardial and epicardial ablation had improved freedom from VT compared with those who underwent endocardial-only ablation (85 % versus 56 %; *P* = 0.03). In a multicenter study by Della Bella et al. [5], 67 % of a subgroup of patients with ischemic VT etiology were in need of a stepwise approach. It could be speculated that an endocardial and epicardial approach as a first-choice ablation strategy in this subgroup might have avoided a substantial number of repeat procedures and improved outcome.

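### Combined-arm patients whose epicardial access fails become screening failures after randomisation, which in its ordinary meaning removes them from one arm only, so the comparison is no longer between the randomised groups

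*Protocol article*

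**What the plan says.** The rule is in the protocol article under Study groups: "When a patient is randomized to the combined approach and the epicardial access is unsuccessful, this is considered a screening failure". The sentence before it reads "Crossover is not allowed during the first procedure".

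Other sections fix when and where the rule applies:

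- Pericardial access: in patients undergoing epicardial ablation, "before ablation and systemic heparinization, subxiphoid pericardial access will be obtained by fluoroscopic guidance". The attempt is part of the index procedure and follows allocation.
- Ablation protocol (both groups): control patients have no access attempt at the index procedure. "If clinical VT is still inducible in the endocardial ablation-only group, an epicardial VT ablation will be performed", and this takes place in a later procedure. No removal rule is attached to it.
- Role of epicardial ablation (Discussion), on a retrospective series: "The pericardial space could not be accessed in 7 % by the percutaneous technique".
- Primary and secondary outcomes: "The secondary outcome parameters will be acute procedure success and procedure-related major complications".
- Statistical analysis: Kaplan–Meier curves and a log-rank test for the primary outcome, with no analysis population named.

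**The concern.** Screening comes before allocation. Failed access comes after it and is a result of attempting the allocated treatment. If these patients leave the comparison, the combined arm holds only patients whose pericardium could be entered. The control arm still holds both kinds, because nobody tested them. Randomisation no longer protects that contrast.

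It is also not the contrast the trial sets out to make. The title and the Study design section of the Discussion describe a choice between two plans: combined approach first, or stepwise. A plan to go epicardial first includes the cases in which the epicardium cannot be reached.

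Two results are at stake. For VT recurrence, the estimated benefit may be that of successful access and not of the strategy. For procedure-related major complications, harm from a failed access attempt belongs to the combined strategy but may not be counted in its arm. The trial is open and access is judged unsuccessful during the procedure, so the rule is applied with the allocation known.

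**Working it through.** **Inputs.** Two-year recurrence is 15 % (combined) and 44 % (control), with 86 evaluable patients and 100 in total (Sample size calculation). Access failure is 7 % (Role of epicardial ablation, another series). Complication rates are 0.6 to 4.1 % (Safety of epicardial ablation). Assumed: 1:1 allocation, so 50 per arm or 43 evaluable; 15 % is the rate among patients with successful access; the recurrence risk of inaccessible patients is not given and is varied.

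**1. The plan's own figure.** HR = ln(0.85)/ln(0.56) = 0.280. Freedman's formula gives 25 events, and 25/0.295 = 84.7, so 85 to 86 patients. Fisher's exact test with 43 per arm has 80.5 % power. The stated 86 is reproduced and is not in dispute.

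**2. How many patients.** 50 × 0.07 = 3.5 expected in the combined arm and none in control. The chance of at least one is 1 − 0.93^50 = 97 %.

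**3. If the treatment works.** As-randomised combined rate = (1 − f) × 15 % + f × r, where f is the proportion failing and r their recurrence risk.

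- f = 7 %, r = 44 %: 13.95 + 3.08 = 17.0 %; contrast 44 − 17.0 = 27.0 points instead of 29.
- f = 7 %, r = 80 % (assumed): 13.95 + 5.60 = 19.55 %; contrast 24.45 points.
- f = 5 % (assumed), r = 44 %: 16.45 %; contrast 27.55 points.
- f = 10 % (assumed), r = 44 %: 17.9 %; contrast 26.1 points.

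By the pooled two-proportion formula at 43 per arm, power is 85.1 % at 15 versus 44 %, and 78.5 % at 17.0 versus 44 %. (This formula is more optimistic than the methods in step 1, so only the drop should be read from it.)

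**4. If the treatment does nothing.** Both arms have 44 % overall. After removal the combined arm shows (44 − f × r)/(1 − f). With f = 7 %:

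- r = 30 %: 41.9/0.93 = 45.05 %, about 1 point against the combined arm.
- r = 44 %: 44 %, no bias.
- r = 60 %: 39.8/0.93 = 42.8 %, 1.2 points in its favour.
- r = 80 %: 38.4/0.93 = 41.3 %, 2.7 points in its favour.

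In simulated log-rank tests (50 per arm, 20,000 trials), removal at f = 7 % gave a two-sided type I error of 5.1 % at r = 60 % and 5.8 to 5.9 % at r = 80 %. False claims favouring the combined arm were 3.1 % and 4.7 %, against 2.5 % nominal. Keeping every patient gave 5.1 to 5.2 % two-sided. The simulation error is about √(0.05 × 0.95/20,000) = 0.15 points. At r = 60 %, therefore, the two-sided figure cannot be told from the nominal level, and only the one-sided split moves.

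**5. Safety.** Expected events in 50 patients: 50 × 0.6 % = 0.3 to 50 × 4.1 % = 2.05. Take 4.1 % after successful access and an assumed 10, 25 or 50 % after failed access. The all-randomised rate is then 0.93 × 4.1 + 0.07 × 10 = 4.5 %, or 5.6 %, or 7.3 %, against 4.1 % with failures left out.

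**The case against.** - **Removal is not spelled out.** The article does not say that these patients go unanalysed, unfollowed or replaced, and a full protocol or SAP may define the populations. This stands as a caution. But exclusion is the ordinary meaning of the term, nothing in the article brings these patients back, and a SAP that analysed them as randomised would have to override a stated rule.
- **A reader might infer that the rule necessarily biases efficacy towards the combined arm.** The documents do not support that. Under no effect, the direction depends on the prognosis of inaccessible patients. The article ties poor access to prior surgery and adhesions (Study population, Limitations), not to a higher risk of VT recurrence. The 60 % and 80 % risks are assumptions. Type I errors above 9 % appear only with 15 % access failure and 80 % recurrence together, and neither has a source in the article.
- **The 7 % may be too high here.** The trial excludes previous bypass surgery, pericarditis and other adhesion risks. This stands. At an assumed 3 % failing and 80 % recurrence, simulated type I error is 5.2 %.
- **The move from 29 to 27 points is mostly dilution, not a false-positive problem.** Correct. It shows that the rule answers a different question from the strategy question posed.
- **A reader might infer that harms of failed access vanish from the trial.** They do not. All serious adverse events must be registered (Adverse events), and a clinical events committee and a safety board review safety (Safety monitoring). What stays open is whether those events count in the between-arm comparison. With 3 to 4 such patients, an assumed 10 to 25 % complication risk means only about 0.35 to 0.9 events.

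**Conclusion.** The point holds in a limited form. The article states a rule that applies after randomisation and to one arm only, and its ordinary meaning is exclusion. The resulting comparison is not between the randomised groups and does not match the strategy question.

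The likely size for efficacy is modest. If the combined approach works, the strategy's benefit is overstated by about 2 points at 7 % failure, given that failures recur at the control rate and that 15 % describes patients with successful access. If it does not work, bias towards the combined arm arises only where inaccessible patients fare worse than average; it is absent at average risk and slightly reversed at lower risk. For safety, the combined arm looks better only to the extent that failed attempts cause complications and these are left out of the arm comparison, which the article does not settle.

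It should be corrected despite the small size. The exclusion follows from the treatment itself, is applied unblinded, and cannot be repaired later if the patients were not followed.

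**What to change.** Replace the sentence under Study groups with, for example: A patient randomised to the combined approach in whom epicardial access fails stays in the combined arm, is followed for 2 years, and is analysed as randomised for the primary, procedural-success and safety outcomes.

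Report the access-failure rate as a result of the combined strategy. Keep an analysis restricted to successful access as a sensitivity analysis only. The change concerns follow-up and analysis, not how these patients are treated.

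The cost is one sentence, the follow-up of about 3 to 4 patients already randomised, and a slightly less favourable expected effect (about 27 instead of 29 points at 7 % failure), which the sponsor may wish to reflect in the power statement.

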### Randomization

Patients are randomized to either the endocardial approach or the combined endocardial and epicardial approach. Randomization is performed using a computer-generated program (ALEA). The person carrying out randomization will not be the treating physician or involved in the selection procedure. The patient and the electrophysiologist who will be performing the procedure will not be blinded for the method of approach.

### Electrophysiology procedure and catheter ablation

#### Pre-procedural preparation

In general, anticoagulation therapy will be discontinued before the procedure (unless the operator decides otherwise). When performing the pericardial puncture, the international normalized ratio should be <2.0. Transthoracic echocardiography will be used to exclude a thrombus in the left ventricle. If the transthoracic echocardiography is inconclusive, contrast transthoracic or transesophageal echocardiography will be used. Antiarrhythmic medications will be stopped 5 days before the procedure. In case of an emergency VT ablation, the operator can choose to do the ablation while continuing antiarrhythmic drugs. Patients who undergo an epicardial ablation will receive general anesthesia; otherwise conscious sedation and local anesthesia will be used. The epicardial ablation is performed with a surgical team as backup.

#### Pericardial access

In patients undergoing epicardial ablation, before ablation and systemic heparinization, subxiphoid pericardial access will be obtained by fluoroscopic guidance (lateral plane). Using a Tuohy needle, small amounts of contrast are injected while carrying out the puncture. Guided by fluoroscopy, a guide wire is inserted into the pericardial space and an Arrow sheath is placed. An appropriate sized guiding catheter is inserted to keep the sheath open. During ablation, we will use an irrigated tip catheter. The baseline flow should be reduced to 1 ml/min. Fluid will be drawn from the pericardial space frequently during the ablation.

At the discretion of the operator, epicardial phrenic nerve capture will be performed if the origin of the VT is located in the area of the phrenic nerve. When capture is performed, a balloon is inserted and inflated to avoid phrenic nerve damage during ablation.

At the end of the procedure, a pericardial drain is inserted for 24–48 h. The operator will administer an intrapericardial steroid injection. Colchicine should be prescribed for up to 1 month, commencing on the first day after the procedure. The first day post procedure Colchicine is dosed 1 mg twice daily followed by a maintenance dose of Colchicine 0.5 mg twice daily.

#### Mapping

Endocardial mapping will be performed in all patients. A multipolar diagnostic catheter will be placed in the coronary sinus. A quadripolar diagnostic catheter will be introduced via the femoral vein to the right ventricular apex. Left ventricle mapping will be performed via the retrograde aortic or transseptal approach. The procedure will be performed under intravenous anticoagulation with heparin, with a target activated clotting time >250 s.

Electroanatomical maps will be obtained using CARTO 3 (Biosense Webster, Diamond Bar, CA, USA) or EnSite NavX (St. Jude Medical, St. Paul, MN, USA). This includes activation (if applicable) and voltage maps. The bipolar voltage thresholds used to consider dense scar and border zone will be 0.5 and 1.5 mV, respectively. We will aim to acquire a very dense map, especially around scar areas. Areas of fractionated or late potentials will be annotated. Programmed ventricular stimulation will be performed, and will involve three extra stimuli from two different right ventricular sites, high-rate pacing, and intravenous isoproterenol (at the discretion of the operator). In hemodynamically unstable VTs mechanical circulation support (Impella, intra-aortic balloon pump) can be considered.

#### Ablation protocol (both groups)

If a hemodynamically tolerated VT is induced during the electrophysiological study, a standard activation or entrainment mapping is carried out. The ablation will continue until the VT is no longer inducible. Additionally, endocardial scar homogenization will be performed. Based on the substrate map, ablation will be empirically extended throughout the entire scar endocardially. Also delayed and fractionated electrograms will be targeted for ablation. If clinical VT is still inducible in the endocardial ablation-only group, an epicardial VT ablation will be performed in a ‘redo’ procedure. Epicardial mapping and ablation will be performed as described in the combined approach.

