### Study design

The study of Di Biase et al. [9] was a retrospective comparison of two techniques. Although there was a well-written prospective protocol, the two well-known techniques are difficult to compare. In the absence of a large scar or in the presence of dense scars, patients did not undergo epicardial ablation. Only 14 out of 43 patients (33 %) in the endocardial and epicardial scar homogenization group underwent epicardial VT ablation. In the current study both groups will undergo scar homogenization. Patients randomized to the combined approach will undergo epicardial ablation unless there is a complete absence of abnormal recordings. The EPILOGUE study is the first randomized controlled study to compare a combined approach with a stepwise approach for VT ablation in patients with ischemic cardiomyopathy.

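### The protocol names two different comparators; its redo rule makes the control arm a stepwise strategy, which the aim, the blanking rule and the planned 44% control rate do not reflect

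*Protocol article*

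**What the plan says.** **Comparator.** The Background gives the aim as finding out whether the combined approach "will improve the outcome of VT ablation in comparison with endocardial scar homogenization only". The abstract's Methods/Design describes the control as "endocardial scar homogenization only (control group"), and the abstract's Discussion sets the same two techniques against each other, though without the word only. The title instead announces "a combined endo-epicardial ablation as the first procedure versus a stepwise approach", and the Study design part of the Discussion calls this the first randomized study "to compare a combined approach with a stepwise approach for VT ablation in patients with ischemic cardiomyopathy".

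**Redo.** Ablation protocol (both groups) says: "If clinical VT is still inducible in the endocardial ablation-only group, an epicardial VT ablation will be performed in a" second procedure, carried out in the way described for the combined arm. Study groups adds: "Crossover is not allowed during the first procedure". No timing is given for the redo, and no corresponding rule is stated for the combined arm.

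**Endpoint and clock.** The primary outcome is recurrence of sustained VT within 2 years. Repeated (epicardial) ablations are listed only among further data. On blanking the protocol says: "We will use a blanking period of 1 week after the ablation procedure". Study design (Methods) and Clinical outcome and follow-up count the 2-year period and the visits from the index procedure.

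**Planning.** Sample size calculation assumes 15% versus 44% recurrence at 2 years, two-sided 5%, 80% power and 86 patients, raised to 100 for dropout.

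**The concern.** The redo is triggered by inducibility at the end of the first ablation, not by a recurrence, so it can come before any primary event. It goes to controls whose first procedure failed by the protocol's own definition, and it gives them the component that distinguishes the experimental arm. A control who fails acutely, has the epicardial redo and then stays free of VT counts as a control without recurrence.

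That is proper for a comparison of strategies. It does not answer whether combined ablation beats endocardial ablation alone. Three things are at stake:

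- **The conclusion.** A null result could be reported as no benefit over endocardial-only ablation when that contrast was not observed.
- **Symmetry of the endpoint.** If a redo opens a new blanking week, the protocol's own rule gives controls, and only controls, extra time in which VT does not count.
- **Power.** A control rate for endocardial ablation alone is too high for a stepwise arm if the redo works.

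**Working it through.** **Step 1: which comparison do the procedures implement?**

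| Place | Control arm is |
|---|---|
| Abstract (Methods/Design), Background | endocardial only |
| Abstract (Discussion) | endocardial, no mention of later steps |
| Title; Discussion, Study design | stepwise |
| Study groups | crossover barred in the first procedure only |
| Ablation protocol (both groups) | endocardial, then epicardial redo if clinical VT stays inducible |

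The two operative sections agree with the title, not with the aim.

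**Step 2: where does the 44% come from?** Role of epicardial ablation reports 12-month freedom from VT of 85% with combined and 56% with endocardial-only ablation, so recurrence is 1 − 0.85 = 15% and 1 − 0.56 = 44%. These equal the planning rates. The sample size section applies them at 2 years and cites a different study, which the Discussion reports as 19% versus 47% with limited endocardial substrate ablation as control. Neither comparator is described as a stepwise arm.

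**Step 3: reproduce the stated 86.** Allocation is not stated; 1:1 is assumed.

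- Fisher's exact test: 42 per arm gives 79.4% power and 43 per arm gives 80.5%, so N = 86.
- Freedman log-rank: HR = ln(0.85)/ln(0.56) = 0.280. Events = [(1.960 + 0.842) × (1 + 0.280)/(1 − 0.280)]² = 24.8, taken as 25. The mean event rate is (0.15 + 0.44)/2 = 0.295, and 25/0.295 = 84.7, or 86 with equal arms.

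The stated number follows from its own inputs.

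**Step 4: allow for the redo.** Let a share f of controls have the redo and then recur at rate r, while the others recur at 44%:

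- control rate p = (1 − f) × 0.44 + f × r
- HR = ln(0.85)/ln(1 − p)
- expected events d = 86 × (p + 0.15)/2
- power = Φ[√d × (1 − HR)/(1 + HR) − 1.96]

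Both f and r are assumptions. Nearby figures in the protocol only help to set a range: epicardial VT in 10% of post-infarction VTs (Background), epicardial ablation in 6% of a post-infarct series (Epicardial ablation in ischemic cardiomyopathy), and 40% of patients needing epicardial ablation for procedural success (Role of epicardial ablation). None is a rate of residual inducibility after endocardial homogenization.

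| f | r | p | HR | d | Power at N = 86 |
|---|---|---|---|---|---|
| 0 | – | 44.0% | 0.280 | 25.4 | 81% |
| 6% | 15% | 42.3% | 0.296 | 24.6 | 77% |
| 10% | 15% | 41.1% | 0.307 | 24.1 | 74% |
| 20% | 15% | 38.2% | 0.338 | 22.9 | 66% |
| 40% | 15% | 32.4% | 0.415 | 20.4 | 46% |
| 10% | 30% | 42.6% | 0.293 | 24.8 | 78% |
| 40% | 30% | 38.4% | 0.335 | 23.0 | 66% |

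Worked line (f = 10%, r = 15%): p = 0.9 × 0.44 + 0.1 × 0.15 = 0.411; √24.1 × 0.693/1.307 = 2.60; Φ(2.60 − 1.96) = 74%.

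**Step 5: what if the redo counted as an event?** If redo and recurrence were independent, the control rate would be 1 − (1 − f) × 0.56, that is 49.6% at f = 10% and 66.4% at f = 40%. The rise comes from a rule that applies to controls alone.

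**The case against.** The best defence is that the arms are defined by the first procedure. The title says so, the aim speaks of a first-line approach, and crossover is barred only in that procedure. On this view the design is coherent and a few sentences are loosely worded. That largely stands. A reader might infer that the trial fails to test any stated comparison; it does test combined-first versus stepwise. Leaving the redo out of the endpoint is legitimate for that question, and redo procedures are recorded. The lack of a matching redo rule in the combined arm is natural, since those patients were already assigned epicardial treatment.

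Three other strong readings are not supported:

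- **That the clock is left open.** The 2-year period and the visits run from the index procedure. Only the effect of a redo is unstated.
- **That blanking hides control failures at large.** The singular wording most naturally means the index procedure. Even on the adverse reading, VT between the end of the first blanked week and a later redo still counts. Detailed redo handling may also sit in documents not shown.
- **That power collapses.** The 40% is a high-end proxy from another setting. So is the 67% that the Discussion gives for an ischemic subgroup needing a stepwise approach. No passage supports 15% recurrence after redo in patients who have just failed acutely.

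What the defence does not remove is the aim as worded, which the procedures cannot answer, and a planning rate with no allowance for the redo. The objective belongs in the protocol and cannot be left to an analysis plan.

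**Conclusion.** The point holds as a contradiction between sections with a moderate, uncertain cost in power. Analysis by randomized arm supports a conclusion about strategies and not about endocardial homogenization alone. The blanking sentence permits, without requiring, an extra uncounted week in controls only.

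The sample size is correct on its inputs, but its 80% power is not shown for the control arm actually planned. Even 6% redo takes the log-rank figure just below 80% if redo patients recur at 15%. The loss is small at low redo shares and substantial only if the redo is both common and effective. These figures rest on 1:1 allocation, 44% recurrence in controls without redo, 15% in the combined arm and 86 evaluable patients.

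This should be fixed, but it does not invalidate the trial.

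**What to change.** 1. Reconcile the abstract and Background with the title, the ablation section and the Discussion by stating one comparison throughout: combined-first versus stepwise strategy, analysed by randomized arm. Limit the conclusion to that.
2. State that time zero and the single blanking week run from the index procedure in both arms, and that a redo neither restarts blanking or the clock nor censors the patient.
3. Restate power as a range over plausible redo shares and post-redo recurrence, as in the table above. The trial need not be enlarged.
4. Report redo procedures by arm descriptively. If a recurrence-or-redo analysis is added, label it as favouring the combined arm: it counts an event that the protocol mandates in controls only, in an unblinded trial, and does not estimate recurrence under endocardial ablation alone.

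The cost is a few sentences and a power table. The data are already to be collected, and enrolment had not begun when the article was written. The price is a narrower claim and an open statement that power may fall below 80%. No change to the clinical redo rule is proposed.
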